Other metabolic processes have also been linked with both obesity and depression. The sirtuins are NAD^+^-dependent protein deacetylases in most cells with known roles in metabolism, the stress response, and aging [44]. Levels of SIRT1 have been found to be low in obesity and aging, and normalization of SIRT1 levels decreases disease effects [44]. Studies have also found that SIRT1 promotes insulin signaling through an anti-inflammatory mechanism and suppresses proinflammatory gene expression in adipocytes [45]. Also, the reverse association between SIRT1 and adipose tissue mass and inflammation was found to be normalized by vitamin D [43].

On the other hand, multiple steps in vitamin D metabolism and function require magnesium as a cofactor, including vitamin D binding to vitamin D binding protein, 25(OH)D synthesis, 1,25(OH)_2_D synthesis, 25-hydroxylase synthesis, and vitamin D receptor expression. In addition, serum 1,25(OH)_2_D levels remain low in individuals with magnesium deficiency even following vitamin D intake [46]. Magnesium deficiency has also been found to reduce parathyroid hormone production and the number of vitamin D receptors in target cells [46].

There is not enough information about the individual effect of vitamin D and magnesium on mood, BDNF, and SIRT1 and about co-supplementation. The aim of this study is to evaluate the effects of vitamin D and magnesium co-supplementation on behavioral measures of mood, circulating BDNF and inflammation-related biomarkers, and levels of SIRT1 in obese women.

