### Objectives and hypotheses of the study

The primary objective of the present study is to assess the effects of vitamin D_3_ and magnesium co-supplementation in obese women on readouts of mood, serum levels of 25(OH)-D, magnesium, BDNF, inflammatory biomarkers (hs-CRP, TNF-α, IL-6), and sirtuin 1 levels. For controlling of confounder factors, the study will evaluate anthropometric indices (weight, body mass index, and waist circumference), dietary intake of energy and macronutrients, and physical activity levels in the women at baseline and at the end of the study.

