### Participants

Participants will be 108 obese women. The inclusion criteria will consist of: BMI = 30–40 kg/m^2^; age = 18–50 years; serum 25(OH)D < 30 ng/ml; serum magnesium ≤ 2 mg/dl; no indication of hormonal changes, autoimmune disease, diabetes, hypertension, or renal, hepatic, parathyroid, hormonal, and gastrointestinal disorders; not pregnant, breast-feeding, or menopaused; not taking vitamin D and/or magnesium supplements and other vitamin–mineral supplements or antidepressant drugs; not taking laxative and/or anti-inflammatory medications; and not having had a weight loss of ≥ 3 kg within 2 months leading up to the trial. Exclusion criteria will be less than 90% compliancy with the treatment.

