### Sample size

To estimate the sample size, we considered α = 0.05 and β = 0.20 in line with previous trials. In addition, we used 1570.5 ng/ml as the standard deviation and 1250.0 ng/ml as the mean of hs-CRP levels as the primary variable, as described previously [47]. This resulted in a requirement of 25 participants in each group. To allow for attrition, 27 participants will be recruited for each group, giving a total of 108 obese women.

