### Statistical analysis

Statistical tests of the outcome measures will be performed using SPSS (version 22.0; SPSS Inc., Chicago, IL, USA). The normality of distribution will be examined and confirmed by the Kolmogorov–Smirnov test. All results will be expressed as mean ± SD. Categorical variables will be presented as frequencies and percentages. The chi-square test will be used to test for differences between categorical variables. Baseline mean differences will be tested using one-way analysis of variance (ANOVA). Analysis of covariance (ANCOVA) will be used to identify differences between the four treatment arms at the end of study, adjusting for baseline values and covariates. The comparison of mean values will be done within groups after the intervention period using paired-sample *t* tests. Bonferroni corrections will be used in pairwise comparisons of the values after the intervention. *P* < 0.05 will be considered statistically significant.

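### For serum 25(OH)D, one pooled residual variance across four arms would miscalibrate the two pairwise contrasts that isolate magnesium, if vitamin D widens the spread in the arms that take it

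*Protocol article*

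**What the plan says.** The Statistical analysis section of the protocol article fixes the model: "Analysis of covariance (ANCOVA) will be used to identify differences between the four treatment arms at the end of study", adjusted for baseline values and covariates, with Bonferroni correction of the pairwise comparisons and significance at 0.05. The only distributional check it names is for normality.

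The Objectives section puts 25(OH)D in the primary objective, among "serum levels of 25(OH)-D, magnesium, BDNF, inflammatory biomarkers" and the other readouts. The Participants section admits only women with "serum 25(OH)D < 30 ng/ml". Under Randomization, two of the four equal arms take weekly vitamin D and the other two take a vitamin D placebo. The Background explains why a combined effect is plausible: "multiple steps in vitamin D metabolism and function require magnesium as a cofactor".

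The trial is not sized on 25(OH)D. The Sample size section uses hs-CRP, and recruitment follows from that: "27 participants will be recruited for each group, giving a total of 108 obese women".

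**The concern.** For 25(OH)D, two arms receive the substance whose serum level is being measured and two do not. All women start below the same cap. In the treated arms, differences between women in how far they respond add to the residual spread, and the untreated arms have no such source of variation. A single residual variance averages the two spreads. It is then too small for a contrast within the vitamin D arms and too large for a contrast within the arms without vitamin D.

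Those two contrasts are the ones that isolate magnesium. Vitamin D plus magnesium versus vitamin D alone asks whether magnesium improves the 25(OH)D response to vitamin D, which is the question the Background raises. At stake is whether its P value and confidence interval mean what they claim. Magnesium alone versus double placebo would lose power for the opposite reason.

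**Working it through.** **1. The plan's own figure.** Inputs from the Sample size section: "we considered α = 0.05 and β = 0.20 in line with previous trials" and "1570.5 ng/ml as the standard deviation and 1250.0 ng/ml as the mean of hs-CRP levels as the primary variable". The 1250.0 is called a mean but works as the difference to detect. Two-sided:

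n = 2 × (1.960 + 0.842)² × (1570.5/1250)² = 24.8, rounded up to 25.

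This agrees with "This resulted in a requirement of 25 participants in each group", and the sample size is not in dispute. Below I assume 25 analysed per arm. Four arm means and one baseline slope leave 100 − 5 = 95 error degrees of freedom.

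**2. Pooled against true standard error.** Let the residual SD after baseline adjustment be σ in the arms without vitamin D and rσ in the arms with it. At equal arm sizes the pooled variance is σ²(1 + r²)/2 on average. Dividing the pooled standard error by the true one gives:

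- Vitamin D + magnesium versus vitamin D: q = √((1 + r²)/2) / r, below 1 for any r > 1.
- Magnesium versus double placebo: q′ = √((1 + r²)/2), above 1 for any r > 1.
- Any vitamin D arm versus any arm without it: 1.

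At r = 2, q = √2.5 / 2 = 0.79 and q′ = √2.5 = 1.58.

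**3. Real error rates.** The error is 2 × (1 − Φ(q × c)), where c is the critical value. Four arms give six pairs, so the Bonferroni level is 0.05/6 = 0.83%. There c = 2.638 from the normal distribution or 2.695 from t with 95 degrees of freedom; these give the two ends of each range in the third column. At r = 2, 0.791 × 2.638 = 2.086 gives 3.7%, and 0.791 × 2.695 = 2.13 gives 3.3%. Coverage and the last column use c = 1.960.

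| r (assumed) | q | D+Mg v D: real error at nominal 0.83% | D+Mg v D: coverage of unadjusted 95% CI | Mg v placebo: real error at nominal 5% |
|---|---|---|---|---|
| 1 | 1.00 | nominal | 95% | nominal |
| 1.25 | 0.91 | 1.5–1.7% | 92% | 2.7% |
| 1.5 | 0.85 | 2.2–2.5% | 90% | 1.2% |
| 2 | 0.79 | 3.3–3.7% | 88% | 0.2% |
| 3 | 0.75 | 4.5–4.9% | 86% | below 0.1% |

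**4. Simulation.** The four-arm ANCOVA was simulated 8,000 times per setting, with baseline truncated at 30 ng/ml and 25 or 27 women per arm. For D+Mg versus D at nominal 0.83%, the error was 2.5–2.7% at r = 1.5, 3.4–3.5% at r = 2 and 4.5–4.9% at r = 3. For magnesium versus placebo at nominal 5%, it was 1.3–1.5% at r = 1.5 and about 0.3% at r = 2.

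**5. Family-wise error.** If vitamin D raises 25(OH)D, the four contrasts of a vitamin D arm with an arm without it are not null. Two nulls remain. Adding their normal-approximation rates at 0.83% bounds the chance of any false positive: 1.69 + 0.28 = 1.97% (r = 1.25), 2.50 + 0.08 = 2.58% (r = 1.5), 3.70 + 0.00 = 3.70% (r = 2) and 4.92 + 0.00 = 4.92% (r = 3). One simulation of 10,000 trials per ratio gave 2.0, 2.7, 3.6 and 4.9%. A second gave 1.9, 2.6, 3.9 and 5.2%, with a Monte Carlo standard error of about 0.2 points at 5%.

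**6. The remedy, at r = 2.** For D+Mg versus D, HC3 standard errors gave 4.8–4.9% at nominal 5% and 0.75–0.84% at nominal 0.83%. An ANCOVA on the two vitamin D arms alone gave 5.1% and 0.74–0.84%. HC3 also brought magnesium versus placebo back to 4.7% at nominal 5%.

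**The case against.** Four objections deserve weight.

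First, no SD for 25(OH)D appears anywhere, and the cap applies at entry only, so values in the arms without vitamin D may pass 30 ng/ml by week 8. This stands. The unequal spread is a reasoned expectation and its size is unknown. But the argument needs only a smaller residual spread in those arms, wherever their values lie.

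Second, a reader might quote the unadjusted error for D+Mg versus D, about 12% at r = 2, and infer that overall error control fails. The documents do not support that reading. Bonferroni is planned, and under it the family-wise error over the two affected contrasts is about 5% or less for r up to 3. What remains is that each contrast is tested at a level other than the one claimed and that the intervals are wrong.

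Third, pooling is not stated in words, and an analysis plan that is not shown may add a remedy. That is fair. Still, one residual variance is how the named method works in its standard form, so the point concerns a stated choice of method.

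Fourth, 25(OH)D is not the variable the trial is sized on, and the protocol does not single out D+Mg versus D on 25(OH)D as a formal hypothesis. Both are true and limit the weight of the point. 25(OH)D is nevertheless listed in the primary objective.

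**Conclusion.** The point holds for serum 25(OH)D only. If residual spread is larger in the vitamin D arms, the pooled model tests vitamin D plus magnesium versus vitamin D alone at about 1.5 to 4.9% where 0.83% is intended, for r from 1.25 to 3. Its unadjusted 95% interval covers about 92% down to 86%. Magnesium versus double placebo is tested at about 0.2–0.3% where 5% is nominal, at r = 2, and so has little chance of showing a modest effect. The direction is certain for any r above 1; the size rests on an assumed r, 25 analysed per arm and six compared pairs.

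Contrasts of vitamin D with no vitamin D are essentially unaffected at equal arm sizes. A reader might extend the concern to hs-CRP, mood, BDNF or SIRT1, but none of these is the substance being given, and the documents offer no comparable reason to expect unequal spread there.

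**What to change.** Add one sentence to the Statistical analysis section: for serum 25(OH)D, pairwise contrasts and their confidence intervals will come from the baseline-adjusted four-arm model with HC3 standard errors or arm-specific residual variances, with the Bonferroni correction kept. Confirm that the named software version offers the option chosen.

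An ANCOVA restricted to the two arms compared is an acceptable alternative that needs nothing beyond ordinary ANCOVA. It is a different estimator, because the baseline slope is fitted in those two arms only, and error degrees of freedom fall from about 95 to about 47 (50 − 3).

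No new data are needed. With HC3 or arm-specific variances, the cost if the spreads prove equal is a slight loss of precision in estimating the variance. The other outcomes need no change on this ground.

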### Randomization

Randomization to the different treatment arms will be performed using computer-generated random numbers. The 108 participants who meet the criteria will be allocated as such into four treatment groups: 50,000 IU vitamin D soft gel (weekly), plus a 250-mg magnesium tablet (daily); 50,000 IU vitamin D soft gel (weekly) plus a magnesium placebo (daily); vitamin D placebo (weekly) plus a 250-mg magnesium tablet (daily); and a vitamin D placebo (weekly) plus a magnesium placebo (daily). The vitamin D soft gels and magnesium tablets are provided by Zahravi, Iran and Jalinous, Iran, respectively. The placebos for vitamin D and magnesium contained oral paraffin and maltodextrin, respectively, and are supplied by Zahravi, Iran (these were matched in appearance of the corresponding soft gels and tablets). Patients will receive verbal and written counseling on how to consume the supplements and compliance will be evaluated by tablet count every 2 weeks.

For blinding, a person who is not involved in the study protocol will create a randomized list assigning participants to each treatment arm. The soft gels, tablets, and corresponding placebos will be placed into unlabeled identical containers. The study leader will label the containers with participant numbers using the codes generated through the randomization. All investigators and participants will be blinded.

Women who meet the inclusion criteria will be informed completely about the protocol of the study. The ethics committee will review and approve the final study protocol. Each participant will sign the informed consent form.

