### Outcome measures

Mood will be assessed using the validated Iranian version of the Beck Depression Inventory (BDI) [48] at baseline and after the intervention period. Blood samples will be collected at both time points after a 12-h overnight fast. Serum will be prepared according to standard protocols and stored at –80 °C until analyses. Serum 25(OH)D will be measured by enzyme-linked immune sorbent assay (ELISA) using the Euro Immun kit (Euro Immun, Germany). Serum magnesium will be determined using a spectrophotometric method with an autoanalyzer (Hitachi 912; Roche Diagnostics). Serum BDNF will be assessed by ELISA using the ZellBio kit (ZellBio, Germany). Serum hs-CRP values will be measured using an immunoturbidimetric method (Pars Azmun, Iran). Serum TNF-α and IL-6 levels will be assessed by ELISA using the Bender Med kit (Bender Med, Germany). Sirtuin 1 will be evaluated using ELISA with the ZellBio kit (ZellBio, Germany).

A questionnaire regarding patient medications and probable supplement use will be recorded at the beginning of the intervention. Dietary intake will be evaluated by 3 days of 24-h recall questionnaires (2 week days and 1 weekend day) at baseline and at the end of the intervention, and total energy and macronutrient intake will be estimated using Nutritionist ӀV software. Physical activity levels will be assessed using the short form of the International Physical Activity Questionnaire (IPAQ) at baseline and at the end of the intervention. Physiometric measures will be taken after overnight fasting, with minimal clothing and without shoes, at baseline and after the intervention. Body weight will be measured with an accuracy of 0.1 kg using the Beurer scale (Beurer, Germany). Height will be assessed using a stadiometer to the nearest 0.5 cm in a standing position without shoes. BMI will be computed as body weight (kilograms) divided by height squared (centimeters squared). Waist circumference will be evaluated at the narrowest point above the hips with an unstretched tape measure.

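### Within-arm paired t tests share the P < 0.05 rule with the between-arm ANCOVA and are not marked as descriptive, although they contain no treatment contrast

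*Protocol article*

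**What the plan says.** The Statistical analysis section of the protocol article names the treatment comparison first: an ANCOVA that "will be used to identify differences between the four treatment arms at the end of study, adjusting for baseline values and covariates". It then adds a second kind of test: "The comparison of mean values will be done within groups after the intervention period using paired-sample" t tests. On multiplicity it says that "Bonferroni corrections will be used in pairwise comparisons of the values after the intervention". It closes with one general rule, that P "< 0.05 will be considered statistically significant". Nothing there describes the paired tests as descriptive or supportive, or says what may be concluded from them.

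Two other sections bear on this. Participants admits only women with "serum 25(OH)D < 30 ng/ml; serum magnesium ≤ 2 mg/dl". Objectives and hypotheses of the study lists as outcomes "readouts of mood, serum levels of 25(OH)-D, magnesium, BDNF, inflammatory biomarkers (hs-CRP, TNF-α, IL-6), and sirtuin 1 levels", so both screened nutrients are also outcomes. Outcome measures sets two measurement times, baseline and after the intervention: "Blood samples will be collected at both time points after a 12-h overnight fast". It does not say whether the sample that qualifies a woman for entry is also her baseline sample.

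**The concern.** A paired test in one arm asks whether that arm's mean changed. Change over 8 weeks combines any treatment effect with time trend, season, taking part in a study and placebo response, and the Beck Depression Inventory, being self-reported, is open to the last of these. The double-placebo arm is there to remove such components, and a within-arm test does not use it. For a variable with an upper entry cut, regression to the mean is a further component.

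At stake is a second route to a statement of significance. An active arm could be reported as significantly changed and placebo as not, while the randomised comparison shows no difference. By its wording the Bonferroni correction covers pairwise comparisons of post-intervention values, so it does not reach these tests.

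**Working it through.** **The plan's own figure.** Sample size gives α = 0.05, β = 0.20, SD 1570.5 ng/ml and 1250.0 ng/ml, and arrives at 25 per group. Taking 1250.0 as a difference between two groups, n = 2 × (1.960 + 0.842)² × (1570.5 / 1250.0)² = 24.8, rounded up to 25, which matches. The trial is thus sized on a between-arm comparison, and the paired tests play no part in it.

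**A change common to all arms, no treatment effect.** Let p be the chance that one arm's paired test gives P < 0.05 (two-sided). Given the common change, the arms are independent. The chance that at least one of the three active arms is significant and placebo is not is

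(1 − p) × [1 − (1 − p)³].

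- p = 0.05 (no change at all): 0.95 × (1 − 0.857) = 0.135, about 14%.
- p = 0.37: 0.63 × (1 − 0.250) = 0.472, about 47%, the maximum.
- p = 0.50: 0.50 × (1 − 0.125) = 0.4375, about 44%.

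The documents give no common change, so its size is assumed. With n = 25 and the change in units of its own SD, the noncentral t distribution gives:

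| Common change (SD) | p per arm | Active significant, placebo not |
|---|---|---|
| 0.1 | 8% | 20% |
| 0.2 | 16% | 34% |
| 0.3 | 30% | 46% |
| 0.4 | 48% | 44% |
| 0.5 | 67% | 32% |
| 0.8 | 97% | 3% |

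The pattern becomes rarer for large common changes because placebo is then significant too.

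**Regression to the mean, 25(OH)D and magnesium only.** Assume that the screening value is the baseline, that values are bivariate normal and standardised in the source population, that a share f lies below the cut c, and that the test-retest correlation is ρ. With λ = φ(c)/f:

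- expected rise in an untreated arm = (1 − ρ)λ
- variance of the change = (1 − ρ²) + (1 − ρ)² × (1 − cλ − λ²)

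Example, f = 0.5 and ρ = 0.5: λ = 0.798; rise = 0.399; variance = 0.75 + 0.25 × 0.363 = 0.841, SD 0.917; standardised change = 0.435. The paired test is then significant in 55% of trials at n = 25 and 59% at n = 27. Across the range, for n = 25 to 27:

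| Share below the cut | ρ = 0.8 | ρ = 0.5 |
|---|---|---|
| 50% | 24–26% | 55–59% |
| 80% | 8–9% | 14–15% |
| 90% | 6% | 8% |
| 95% | 5% | 6% |

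**The planned ANCOVA under the same conditions.** In simulations with no treatment effect and 25 per arm (3000 runs each), the four-arm baseline-adjusted F test rejected in 4.2% of trials (50% below the cut, ρ = 0.7) and 5.3% (70% below, ρ = 0.8), in line with the nominal 5%. In the first of these settings a single arm's paired test was significant in 34% of trials (p = 0.336 before rounding). The formula above then gives 0.664 × (1 − 0.293) = 47% for an active arm significant and placebo not.

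**The case against.** The strongest reply is that the protocol never says a paired result will be read as efficacy. Its treatment comparison is the ANCOVA, in a double-blind trial with a double-placebo arm, and a significant change within an arm is a true statement about change. This stands. A reader might infer that the plan relies on within-arm tests for efficacy, or lacks a between-arm analysis; the text supports neither.

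A second reply is that the role of supportive tests may be set out in an analysis plan that is not shown. This carries less weight. The article does more than stay silent: it names the tests, and its one significance rule covers them.

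A third reply concerns the size of the problem, and most of it stands. A reader might infer that regression to the mean affects all the outcomes. The entry cuts act directly only on 25(OH)D and magnesium; mood, BDNF, hs-CRP (the sample-size variable), TNF-α, IL-6 and SIRT1 have none. Even for the two nutrients it depends on the screening value being the baseline, and it nearly vanishes if most of the source population lies below the cut. The documents settle neither point.

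A reader might also count 8 outcomes in 4 arms as 32 tests and quote 1 − 0.95³² = 81% for at least one false positive. That figure includes the placebo arm and changes in the unfavourable direction, and it assumes independent outcomes. Counting only favourable changes in active arms gives 24 tests at 0.025: 0.6 expected, and 1 − 0.975²⁴ = 46% for at least one, still assuming independence, which is doubtful for related inflammatory markers in the same women.

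**Conclusion.** The point holds as a fault in a stated analysis choice. The paired tests are given a significance rule but no defined role, and they can yield significant results without any treatment effect. For any one outcome, an active arm is significant and placebo is not in about 14% to 47% of null trials while the per-arm chance of significance lies between 5% and 50%. Where in that range the trial falls depends on a common change that the documents do not quantify.

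For 25(OH)D and magnesium the added risk from regression to the mean runs from negligible to large, according to the share of the source population below the cut and the test-retest correlation, and only if screening and baseline values coincide.

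The randomised comparison, its type I error and the 25 per group are sound on this point. The weakness lies in what the wording permits in reporting, so the change is worth making but the design is not in question.

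**What to change.** Replace the sentence on paired t tests with one that reports within-arm change descriptively, as mean change with SD or 95% CI and no P value. Add that all efficacy conclusions rest on the baseline-adjusted between-arm contrasts from the ANCOVA.

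The cost is one or two sentences of analysis wording. No data, participants or power for the randomised comparison are lost, and recruitment stays at 27 per group, 108 in total.
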